#### Cost -effectiveness analysis (CEA)

The outcome of the CEA is the incremental cost-effectiveness ratio (ICER) of the blended physiotherapy program compared to the usual care program. The ICER is calculated as incremental costs divided by incremental effects. The analysis thus consists of two components: (1) incremental costs and (2) the incremental health outcomes (effects).

##### Costs

In accordance with the European Network for Health Technology Assessment (EUnetHTA) guidelines, the CEA will comprise two parts: a base case analysis, which only takes into account direct medical costs, and an extended analysis, which additionally considers relevant indirect costs such as work absenteeism and productivity loss [68]. As all relevant direct medical costs (i.e. consultation fees, scans, medication, etc.) stem from inpatient care provision, the costs for the base case analysis will be collected using the financial records of the Antwerp University Hospital. Relevant medication use is registered as a standard practice in the RCT described above. To assign costs to medication use, we will use the official unit prices of the Rijksinstituut voor Ziekte- en Invaliditeitsverzekering (RIZIV)/ l’Assurance soins de santé et indemnités (INAMI). As discussed above, patients are allowed to seek medical help outside the hospital between the two follow-up moments. As a consequence, healthcare and medication use cannot be monitored using hospital’s financial records in this period of time. Therefore, patients will keep a diary specifically designed for this study in which they should report all information regarding tinnitus related medical help and medication use. The content of this diary is discussed elaborately above.

Apart from the direct medical costs, the CEA will also incorporate relevant indirect costs in a separate, extended analysis. The abovementioned *i*PCQ will be used to collect the necessary input to calculate the costs associated to absenteeism and productivity loss due to tinnitus complaints following the Human Capital Approach (HCA) [68]. The HCA values the time during the whole period of work inability due to sick leave by multiplying the total number of days of work absenteeism by the national average labour cost per day. To calculate the productivity loss at work, the number of days with productivity loss will be multiplied by efficiency loss and the daily average of hours worked. Next, to value the productivity loss, this result will be multiplied by the national average labour cost per hour. All cost data will be collected over the entire study period starting at baseline.

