##### Diary of medical costs

As patients are allowed to seek medical help outside the participating hospital between the 1 month and 3 months follow-up visits, healthcare/medication use cannot be monitored using the hospital’s financial records. Therefore, patients will be handed a diary in which they should collect all information regarding tinnitus related medical help, such as physician consultations (including general practitioners), psychological consultations, medication use and treatments in the context of their tinnitus complaints.

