#### Blended physiotherapy program (experimental treatment)

The experimental group will receive a blended physiotherapy program consisting of only six instead of twelve physiotherapy treatments over a period of 12 weeks, meaning one treatment session of 30 min every 2 weeks. In addition, a smartphone application will offer the patients a daily exercise program, based upon the standard physiotherapy treatment for ST [14–22], and psychological tinnitus counselling. This tinnitus counselling program consists of two sessions a week and is developed by psychologists of the University of Regensburg [64, 65]. Before the start of the program, the exercises will be tailored to the area, type and degree of the patient’s dysfunctions. During the six physiotherapy treatment sessions, patients will, if needed, receive manual mobilisations to increase mobility of the neck and/or temporomandibular joints or manual techniques to decrease muscle tension in neck and jaw muscles [14–22]. Additional counselling on knowledge about neck and jaw pain and advice about posture and movement habits will also be provided by the physiotherapist during these six treatment sessions.

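### The named cost sources identify no cost for the app and its counselling programme, yet the costing section says inpatient care covers all direct medical costs

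*Protocol article*

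**What the plan says.** The cost-effectiveness analysis in the protocol article has two parts. The first is "a base case analysis, which only takes into account direct medical costs"; the second is an extended analysis that adds absenteeism and productivity loss. The Costs section justifies its data source by asserting that "all relevant direct medical costs (i.e. consultation fees, scans, medication, etc.) stem from inpatient care provision", and concludes that "the costs for the base case analysis will be collected using the financial records of the Antwerp University Hospital".

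Two further sources are named:
- For medication: "To assign costs to medication use, we will use the official unit prices".
- For care sought outside the hospital between the 1-month and 3-month visits: "patients will keep a diary specifically designed for this study in which they should report all information regarding tinnitus related medical help and medication use". Its content is listed in the section Diary of medical costs as "physician consultations (including general practitioners), psychological consultations, medication use and treatments in the context of their tinnitus complaints".

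The intervention sections describe what differs between the arms. The experimental arm has "only six instead of twelve physiotherapy treatments over a period of 12 weeks". In addition, "a smartphone application will offer the patients a daily exercise program", together with two tinnitus counselling sessions a week from a programme written at another university. The control arm has twelve weekly sessions and no tinnitus counselling.

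**The concern.** The costing section states a reason for its choice of data source, and that reason does not match the intervention. Both arms are treated in clinic sessions weekly or fortnightly, and the experimental arm also uses an app between sessions. The app and its counselling are what the trial sets out to evaluate, but they appear nowhere as a cost item and have no named source or unit price.

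Cost-effectiveness is one of the trial's two aims, and the Background hypothesises lower direct and indirect costs. The clinical hypothesis is that the blended programme is at least as effective as standard care. The QALY difference may therefore be small, and the cost difference may decide the economic conclusion. A cost that falls on one arm only and has no entry point in the analysis matters in that setting.

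**Working it through.** **The plan's own figure.** The cost-effectiveness sections state no fee, app cost, QALY difference or ICER, so there is nothing to reproduce. What can be checked is whether each named source reaches the app, and what follows if none does.

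**Step 1: sources against the app.**

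| Source | What it covers | Identifies app or counselling cost? |
|---|---|---|
| Hospital financial records | Consultation fees, scans, medication and similar items, framed as inpatient care | Not stated; a licence entry is possible but none is mentioned |
| Official unit prices | Medication | No |
| Patient diary | Consultations, medication and treatments between the 1-month and 3-month visits, after the treatment programme has ended | No |
| iPCQ (extended analysis) | Absenteeism and productivity loss | No |

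The planned bootstrap describes sampling uncertainty in the costs that were entered. It cannot reveal a cost that was not.

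**Step 2: effect of an omitted cost.** Let f be the fee per session, c the per-patient cost of app and counselling, and r the difference in all other direct costs (unknown before the trial). The arms differ by 12 − 6 = 6 sessions.

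- With the app costed: ΔC = −6f + c + r
- Without it: ΔC = −6f + r
- Understatement of incremental cost: c

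For any willingness to pay λ, incremental net benefit is λ·ΔQALY − ΔC. Omitting c therefore raises it by exactly c in favour of the experimental arm, whatever the sign of ΔQALY.

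**Step 3: break-even.** Setting r aside, the session saving is cancelled when c = 6f. The fees are assumptions:

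| Assumed f (euro) | 20 | 25 | 30 | 40 | 50 |
|---|---|---|---|---|---|
| Break-even c = 6f (euro) | 120 | 150 | 180 | 240 | 300 |

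**Step 4: illustration on the ICER.** Assume f = 30 euro, r = 0 and ΔQALY = +0.01:

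- c = 0: −180/0.01 = −18,000 euro per QALY (cheaper and better)
- c = 100: −80/0.01 = −8,000
- c = 200: +20/0.01 = +2,000
- c = 400: +220/0.01 = +22,000

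**Step 5: dependence of c on the number of users.** Assume fixed app costs of 50,000 to 200,000 euro.

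- Spread over the 167 patients of the experimental arm: 50,000/167 = 299 and 200,000/167 = 1,198 euro each.
- Spread over an assumed 5,000 users: 50,000/5,000 = 10 and 200,000/5,000 = 40 euro each.

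At fees of 25 to 40 euro (a saving of 150 to 240 euro), the first spread reverses the saving and the second does not.

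**The case against.** The strongest defence is that this is a condensed article and that unit costing usually belongs in a fuller protocol or health-economic plan. The list of direct costs is left open, financial records can be broader than patient billing and may hold a licence or supply charge, and incremental cost is defined for the blended programme as a whole, which includes the app. The word inpatient may loosely mean care given in the hospital, since the same section contrasts it with care sought elsewhere.

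Much of this stands as a limit on what can be claimed. A reader might infer that direct costs come from hospital records alone, but medication prices and the diary are also named. A reader might infer that the app is entered at zero cost and that the ICER is therefore shown to be biased. No section says the app is free or excluded, so the bias is conditional. A reader might also count exercise tailoring as a cost of the experimental arm only, but the control programme is individually tailored too. Only the session count is fixed by design to favour the experimental arm; the direction of other consultations, scans and medication is unknown. Whether development and certification costs belong in a trial-based evaluation is open to debate.

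The defence does not remove the point itself. The article does more than leave detail out: it states that one kind of care accounts for all relevant direct costs, and it chooses its main source on that ground. The open-ended list does not help, because the whole list is confined to inpatient care.

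**Conclusion.** The concern holds in conditional form. The stated premise is wrong for an app-supported programme delivered in clinic sessions, and no named source in either analysis identifies a cost for the app and counselling. If the sources are used as written and the hospital records contain no app charge, incremental cost is understated by c, in favour of the experimental arm.

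The size of c cannot be obtained from the article. The session saving reverses only if c exceeds six session fees. Whether it does depends on assumed fees, assumed fixed costs and the number of users sharing them, and across the ranges shown it goes both ways. The tempting conclusion that a saving is built into the comparison is therefore not supported. The primary analysis of the TFI is unaffected.

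**What to change.** - Remove the statement that all relevant direct medical costs arise from inpatient care.
- Add an explicit intervention-cost line for app and counselling to the base case and the extended analysis: licence or running cost, hosting, maintenance, user support, and any app-specific therapist time beyond the tailoring done in both arms. Name the source of each item. If the hospital records do hold an app charge, say so and make sure it is counted once.
- Present a sensitivity analysis with and without development costs, and over a range for the number of users sharing fixed costs.

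This takes a little more costing work and a change of wording before analysis; it needs no new patient-level data. The stated saving may become less favourable.

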##### Health outcomes

To evaluate the potential health gains of ST patients due to the blended physiotherapy program, this study will employ quality-adjusted life years (QALYs). QALYs combine both length of life (LoL) and health-related quality of life (HRQOL) in one composite measure. One QALY gained because of the blended physiotherapy program can thus be interpreted as living one additional year in perfect health due to the proposed treatment.

HRQOL will be determined using the EuroQoL EQ-5D-5L questionnaire, which is discussed elaborately above. While we expect HRQOL to be equal across groups at visit 1, data collection at baseline is necessary to be able to adjust for possible, but unlikely, baseline differences between the control group and intervention group. The resulting health states will be converted into health utilities (ranging from 0 to 1 with 0 equal to death and 1 to perfect health) using the recently published utility value sets for Belgium and will at its turn be used to calculate QALYs [61]. Next, incremental health gains will be calculated by comparing the QALYs of the intervention group to the control group.

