**Methods:**

This study is designed as a single-blind two-arm 1:1 randomised controlled trial (RCT). Adult patients diagnosed with ST, without psychiatric comorbidities and with experience in using a smartphone, will be recruited at the Ear Nose Throat (ENT) department of the Antwerp University Hospital (UZA). Patients will be randomised into two groups. The experimental group will receive the blended physiotherapy program comprising six in-clinic physiotherapy sessions over a period of 12 weeks (1x/2 weeks) and an exercise and counselling program provided by the smartphone application. The control group will receive the standard care program comprising twelve weekly in-clinic physiotherapy sessions. Each physiotherapy session has a duration of 30 min. The primary outcome measure is the change in Tinnitus Functional Index (TFI) score. Additionally, a cost-effectiveness analysis will be performed from a societal perspective considering both direct and indirect costs. There will be follow-up assessments at one and 3 months after the final treatment session.

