### Study design and randomisation procedure

The study is designed as a single-blind two-arm 1:1 randomised controlled trial. After baseline measurements, patients will be randomised into either the experimental group or the control group. A stratified randomisation according to the grade of tinnitus severity obtained by use of the Tinnitus Functional Index (TFI) and gender will be used. The TFI categorises patients from grade 1 (no tinnitus distress) to grade 5 (very severe tinnitus distress) [33–35]. Only grades 2–5 are considered for this study: light distress (7 to 28), moderate distress (29 to 47), severe tinnitus distress (48 to 65) and very severe tinnitus distress (66 to 100) [35]. The stratified randomisation assures an even distribution of patients of each tinnitus grade and of men and women in both treatment arms. A minimisation procedure will be used to perform the stratified randomisation using the web-based online randomisation tool Qminim [36]. Patients will be informed that the study investigates the effectiveness of two different physiotherapy approaches for ST but will not receive in-detail information about the content of the treatment before randomisation. Hence, patients are blinded towards the group they are randomised to. The therapist cannot be blinded. To limit the risk of bias related to lack of blinding of the therapist, all evaluation measurements will be performed by a blinded assessor and data analysts will be blinded as well. An overview of the study design and randomisation procedure is presented in Fig. 1.

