### Outcome measures

The following outcome measures will be collected at baseline and during the two follow-up visits. The first follow-up visit is planned 1 month (range: 4 to 7 weeks) after the last treatment session. The second follow-up visit will take place 3 months (range: 8 to 13 weeks) after the last treatment session. In between the first and second follow-up moment should be a minimum period of 4 weeks. For certain outcome measures additional measuring moments are planned, these are specified individually below. See Fig. 2 for an in-detail schedule of enrolment, interventions and assessments in accordance with the SPIRIT 2013 guidelines [30].

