##### Questionnaires related to the cost-effectiveness analysis

EuroQoL (EQ)-5D [58]

The EuroQoL EQ-5D questionnaire is the most commonly used method to collect health-related Quality of Life (HRQOL) data and is recommended by worldwide economic evaluation guidelines such as the NICE recommendations [59, 60]. This questionnaire measures HRQOL using 5 dimensions: mobility, self-care, usual activities, pain/discomfort and anxiety/depression [58]. The response pattern produces a code which represents a health state of the participant. Each health state is associated with a health utility value between 0 and 1 in which 0 represents death and 1 corresponds to perfect health [60]. To calculate utility values, the recently published utility value sets for Belgium will be used [61]. HRQOL is necessary to calculate quality-adjusted life years (QALYs), the most important outcome from the health economics point of view [60]. The five level (5 L)-version is preferred over the three level (3 L)-version as it is more nuanced and thus more sensitive to gains (or losses) in general health [62]. The EQ-5D-5L will be assessed at baseline and both follow-up moments and will additionally be collected after the final treatment session.Productivity Cost Questionnaire (*i*PCQ) [63]

The iMTA Productivity Cost Questionnaire (*i*PCQ) includes three modules measuring productivity losses of paid work due to (1) absenteeism and (2) presenteeism (productivity loss due to paid work) and productivity losses related to (3) unpaid work. The *i*PCQ delivers the necessary input to calculate productivity loss. *i*PCQ will be collected monthly, meaning every 3 to 5 weeks. To organise this systematically, patients of the intervention group will be asked to complete this questionnaire at treatment session two, four and six and patients of the control group at treatment session four, eight and twelve. Both groups will additionally receive the *i*PCQ at 1 month follow-up and 3 months follow-up, as defined above. An additional two-month follow-up moment is planned for the *i*PCQ (range: 3 to 5 weeks after 1 month follow-up assessment).

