#### Cost-effectiveness

Finally, the ICER will be calculated by dividing incremental costs by incremental health gains and is by consequence expressed as €/QALY gained. This outcome can thus be interpreted as the additional amount of costs needed for the blended physiotherapy program to gain one additional QALY compared to the usual care program. The robustness of the results will be assessed by bootstrapping (> 1000 samples) and be presented on a cost-effectiveness plane. The results will consist of a base case analysis taking into account only the direct medical costs and an extended analysis taking into account both direct and indirect costs.

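### The incremental QALY should be adjusted for baseline EQ-5D-5L utility in every case; the plan treats baseline imbalance as unlikely and does not commit to adjustment

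*Protocol article*

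**What the plan says.** The Health outcomes section of the cost-effectiveness analysis gives one reason for measuring EQ-5D-5L at baseline. It opens with "While we expect HRQOL to be equal across groups at visit 1" and goes on to say that baseline collection is "necessary to be able to adjust for possible, but unlikely, baseline differences between the control group and intervention group". The estimator follows: "incremental health gains will be calculated by comparing the QALYs of the intervention group to the control group". No baseline term appears in that sentence. The Cost-effectiveness section then divides incremental costs by incremental health gains and adds a bootstrap of more than 1000 samples, shown on a cost-effectiveness plane.

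Three other places bear on the point:

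- Study design and randomisation procedure: "A stratified randomisation according to the grade of tinnitus severity obtained by use of the Tinnitus Functional Index (TFI) and gender will be used", carried out by minimisation. Utility is not a balancing factor.
- Questionnaires related to the cost-effectiveness analysis: "The EQ-5D-5L will be assessed at baseline and both follow-up moments and will additionally be collected after the final treatment session". That makes four utility measurements per patient.
- Sample size and power: 150 analysable patients per arm, with 167 recruited per arm to allow for 10% drop-out.

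**The concern.** Randomisation equalises baseline utility in expectation, not in the sample that is drawn. Describing a difference as unlikely, and presenting adjustment as the answer to that unlikely event, invites an analyst either to compare raw QALYs or to decide on adjustment after looking at the baseline table.

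Baseline utility matters to a QALY in two ways. It is the first point of each patient's area under the utility curve, and it predicts the later points. A chance difference at baseline therefore carries through to the incremental QALY unless it is adjusted for. Including baseline in the area does not correct the imbalance; it is one of the routes by which the imbalance enters.

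The incremental QALY is the denominator of the ICER, and cost-effectiveness is one of the trial's two stated aims. If the true QALY difference is small, avoidable noise in the denominator can affect its sign and the quadrant in which the result falls. Bootstrapping unadjusted QALYs displays that uncertainty correctly but does not reduce it.

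**Working it through.** **The plan's own figure.** Margin 6.5, SD 20, one-sided α 0.025, power 80%: n = 2 × (1.960 + 0.842)² × 20² / 6.5² ≈ 148.6, so 149 per arm by the normal approximation. With the t-test, power is 79.8% at 149 and 80.1% at 150, so 150 is right. 150 / 0.90 = 166.7, so 167 per arm and 334 in total. The plan reproduces. It gives no SD, correlation or expected effect for utilities or QALYs, so the inputs below marked as assumed are mine.

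**Step 1: how likely is a baseline imbalance?** SE of the difference in mean baseline utility = SD × √(2/150), with the utility SD assumed.

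| Assumed SD | SE | P(abs. difference > 0.01) | P(abs. difference > 0.02) |
|---|---|---|---|
| 0.15 | 0.0173 | 56% | 25% |
| 0.20 | 0.0231 | 67% | 39% |
| 0.25 | 0.0289 | 73% | 49% |

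These ignore any help from minimisation. If TFI grade and gender together correlated 0.5 with utility (assumed) and were perfectly balanced, the SE at SD 0.20 would become 0.0231 × √(1 − 0.25) = 0.020. The two probabilities would fall to about 62% and 32%.

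**Step 2: how strongly does baseline determine the QALY?** Treatment lasts 12 weeks ("six in-clinic physiotherapy sessions over a period of 12 weeks" in the experimental arm). The first follow-up is "1 month (range: 4 to 7 weeks) after the last treatment session", and the second is 8 to 13 weeks after that session. I take visits at weeks 0, 12, 16 and 25, so T = 25/52.18 = 0.479 years. The trapezoid weights are:

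- baseline: 12/50 = 0.24
- end of treatment: (12 + 4)/50 = 0.32
- first follow-up: (4 + 9)/50 = 0.26
- second follow-up: 9/50 = 0.18

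The sum of squared weights is 0.26. Assume equal SDs at each visit and a common between-visit correlation ρ. In units of SD:

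- covariance of baseline with time-averaged utility: c = 0.24 + 0.76ρ
- variance of time-averaged utility: v = 0.26 + 0.74ρ
- share of QALY variance explained by baseline: R² = c²/v
- SE unadjusted = T × SD × √v × √(2/150); SE adjusted = SE unadjusted × √(1 − R²)
- slope of QALY on baseline utility = T × c

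At ρ = 0.3: c = 0.468, v = 0.482, R² = 0.219/0.482 = 0.45. At ρ = 0.7: c = 0.772, v = 0.778, R² = 0.596/0.778 = 0.77.

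| Assumed ρ | R² (variance removed by always adjusting) | SE unadjusted (SD 0.20) | SE adjusted | Shift in unadjusted QALY difference from a 0.02 imbalance |
|---|---|---|---|---|
| 0.3 | 0.45 | 0.0077 | 0.0057 | 0.0045 |
| 0.5 | 0.61 | 0.0088 | 0.0055 | 0.0059 |
| 0.6 | 0.69 | 0.0093 | 0.0052 | 0.0067 |
| 0.7 | 0.77 | 0.0098 | 0.0047 | 0.0074 |

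R² does not depend on the assumed SD. Moving the visits within their permitted windows (second follow-up at week 20 to 25, first at week 16 or 19) changes it little: 0.44 to 0.51 at ρ = 0.3, and 0.76 to 0.79 at ρ = 0.7.

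**Step 3: what if adjustment followed only an observed imbalance?** The protocol states no trigger. For illustration, 8000 trials were simulated with visits at weeks 0, 12, 16 and 24 and adjustment only when the baseline difference had p < 0.05. The SEs (never / only if p < 0.05 / always) were 0.0084 / 0.0077 / 0.0052 at ρ = 0.5 and 0.0094 / 0.0083 / 0.0045 at ρ = 0.7. Relative to never adjusting, the trigger removes about 17% and 22% of the variance, against about 61% and 78% for always adjusting. All three estimators averaged close to zero, the true value in the simulation.

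**The case against.** The strongest reply is that the section explains why baseline is collected, not how it is analysed. It already foresees adjustment, and its one-line description of the comparison does not exclude a regression. A condensed article may leave the model to the full protocol or a health-economic plan. Much of this stands. The absence of a model specification is not the point here, and if the full plan adjusts in every case nothing is lost.

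Three stronger readings are tempting and should not be drawn:

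- A reader might infer that baseline utility is used only if the groups turn out to differ. No sentence says so, and no test or threshold is given; the wording is compatible with adjusting always.
- A reader might infer that chance imbalance biases or drives the result. The unadjusted comparison is unbiased over randomisation, and the bootstrap would show its uncertainty honestly. Nor does the protocol say that the QALY difference is near zero: its no-difference hypothesis concerns TFI.
- A reader might infer that most of the attainable precision is given up. That needs a plan that never adjusts, or one with a trigger, together with correlations that the protocol does not state. At ρ = 0.3 the share is below half.

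The reply does not rescue the printed premise. The section calls imbalance unlikely, ties adjustment to it, and then states a comparison without a baseline term. Someone following that text would default to an unadjusted or imbalance-dependent analysis.

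**Conclusion.** The point holds in limited form. The premise that baseline differences are unlikely is wrong at 150 per arm: a difference in mean utility above 0.02 has a probability of about 25% to 49% for an assumed SD of 0.15 to 0.25, somewhat less if the minimisation factors predict utility. The text does not commit to using baseline utility in the comparison. If it were never used, the cost would be precision and accuracy given the observed imbalance, not systematic bias: about 45% (ρ = 0.3) to 77% (ρ = 0.7) of the variance of the incremental QALY would be avoidable. These shares rest on equal SDs, a common between-visit correlation and trapezoid QALYs over about 25 weeks. A rule based on observed imbalance would recover only a part, roughly a quarter in the simulated example. The primary TFI analysis and its sample size are not affected. This is a worthwhile improvement at almost no cost rather than a threat to the trial's validity.

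**What to change.** In the Health outcomes section, delete the phrase that calls baseline differences possible but unlikely, and replace the sentence on incremental health gains with wording such as: *Incremental QALYs are estimated by regression of each patient's QALY on treatment arm and baseline EQ-5D-5L utility, with TFI grade and gender as further covariates, in every case and whatever the observed baseline difference. The regression is refitted in each bootstrap sample. The unadjusted difference is reported as a sensitivity result.*

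The cost is a sentence or two of text and a few lines of code. Baseline EQ-5D-5L, TFI grade and gender are already collected, so no data collection changes. The wording should be fixed before baseline data are compared by arm.
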